## Abstract

**Background:**

Exposure to secondhand smoke (SHS) early in life increases the risk of sudden infant death syndrome (SIDS), asthma, and respiratory illnesses. Since children’s primary exposure to SHS occurs in the home, these most vulnerable members of our society are not fully protected by recent increases in the adoption of smoking bans in public spaces. Although exposure to SHS is a quickly reversible cause of excess morbidity, few low-income homes strictly enforce smoking restrictions.

**Objective:**

This study aims to test a novel approach to motivate the adoption of home smoking restrictions and to eliminate child SHS exposure by providing parents with objective data documenting home SHS exposure and “biomarker feedback” of child ingestion of tobacco toxins, that is, objective, laboratory-based results of assays performed on child urine, documenting levels of nicotine; cotinine; and NNAL (4-[methylnitrosamino]-1-[3-pyridyl]-1-butanol), which is a metabolite of the known tobacco carcinogen NNK (4-[methylnitro-samino]-1-[3-pyridyl]-1-butanone).

**Methods:**

From 2011 to 2013, 195 low-income, female smokers with children aged ≤10 years residing in their homes were recruited into a two-arm randomized clinical trial. Participants were assigned to one of two groups: biomarker feedback (n=98) and health education (n=97). In-home assessments were administered at baseline, week 16, and week 26. Children’s home SHS exposure and nicotine, cotinine, and NNAL levels from urine samples, measured through a passive nicotine dosimeter and a surface sample of residual tobacco smoke (ie, thirdhand smoke), were collected at all three time points. Primary outcome was dosimeter-verified, self-reported complete home smoking restrictions at 6 months after randomization. Secondary outcomes included parental self-report of smoking behavior change and child urine tobacco toxin (biomarker) change.

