## Methods

### Study Design

Figure 1 presents an overview of the study. The primary aim of this two-group, community-based randomized trial (ClinicalTrials.gov NCT01574560) was to assess the efficacy of providing mothers with biomarker feedback documenting their child’s tobacco toxin exposure on reduction of home exposure to tobacco toxins. Once eligibility was determined, participants were randomized to either the intervention arm (biomarker feedback) or the control arm (health education). At baseline, participants in both groups received a series of health education brochures designed to provide information on the dangers of SHS and THS, strategies for managing parenting stress, and tips to assist in a quit attempt. Participants randomized to the active condition were given the results of their child’s urine analyses of nicotine, cotinine, and NNAL as well as the results of the home nicotine dosimeter. They also received five motivational interviewing counseling sessions, approximately 30 minutes in length, spread over 12 weeks. At each counseling session, participants were offered nicotine replacement therapy in the form of gum or lozenge (4 mg). The primary outcome was reduction in home ambient nicotine levels, objectively measured by the passive nicotine dosimeter [31] at 6 months after randomization. Secondary outcomes included child exposure to tobacco toxins measured by urinary levels cotinine, nicotine, and NNAL (a metabolite of NNK, which is a tobacco-specific carcinogen known as 4-[methylnitro-samino]-1-[3-pyridyl]-1-butanone) and a parental report of cigarettes smoked in the home and home smoking policies. Additional aims included identifying potential mediating and moderating effects of demographic variables and psychosocial and tobacco use characteristics.

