### Outcomes

#### Primary and Secondary Outcomes

The primary outcome for this study is change in home SHS exposure measured by the passive air nicotine dosimeter at 26 weeks poststudy enrollment. The specificity of the nicotine dosimeter as a marker of SHS is an appropriate marker to measure a reduction in home air nicotine. Reduction in child’s cotinine and NNAL levels and parental report of smoking behavior change (ie, cessation, quit attempts, reduction, and restrictions) served as secondary outcomes. Specifically, carbon monoxide–verified, 7-day, self-reported point-prevalence abstinence assessed 6 months after study enrollment and defined as no smoking, not even a puff, for 7 consecutive days prior to the final assessment point at month 6 served as the smoking cessation measure [47]. Using a conservative approach, participants who dropped out or were lost to follow-up were considered to be smoking. Adoption of home smoking restrictions was assessed by a question modified from the Current Population Survey Tobacco Use Supplement [48]: “Which statement best describes the rules about smoking in your home?” Participants reported whether there were no bans (“Smoking is permitted anywhere”), some restriction (”Smoking is allowed in some places or at some times”), or complete restriction or ban (“No one is allowed to smoke anywhere”). Smokers were also asked to report the number of cigarettes smoked per day and the number of quit attempts in at least 24 hours since enrollment and their use of programs (eg, Helpline) or pharmacological therapy (eg, nicotine replacement therapy and other cessation medications) at weeks 8 and 26.

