#### Sample Size and Power Considerations

The sample size was chosen to ensure adequate power in order to examine the efficacy of tobacco-specific biomarker feedback in terms of the difference of SHS home exposure (primary outcome) between the two treatment groups at week 26. The power calculation was based on two-sided, two-sample *t* test assuming a type I error of 0.05. A total sample size of 180 (90 per treatment group) was determined to achieve 85% power in order to detect an expected difference (between 1.15 [SD 1.58] μg/m^3^ for the biomarker feedback group and 1.89 [SD 1.68] μg/m^3^ for the health education group) in air nicotine levels measured by dosimeters, which was derived from the assumed adoption rates of home smoking bans of the two treatment groups (55% vs 25%).

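### The abstract names a binary home smoking restriction as the primary outcome, while the body and the only power calculation use dosimeter-measured home air nicotine

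*Protocol article*

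**What the plan says.** The Methods paragraph of the abstract states: "Primary outcome was dosimeter-verified, self-reported complete home smoking restrictions at 6 months after randomization". Its secondary outcomes are parental self-reported behavior change and child urine biomarkers. Air nicotine is not listed there as an outcome of its own; in the outcome definition the dosimeter serves only to verify the reported restriction.

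The body says otherwise:

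- Study Design: "The primary outcome was reduction in home ambient nicotine levels, objectively measured by the passive nicotine dosimeter", at 6 months after randomization. Its secondary outcomes include "a parental report of cigarettes smoked in the home and home smoking policies".
- The Outcomes section states: "The primary outcome for this study is change in home SHS exposure measured by the passive air nicotine dosimeter at 26 weeks poststudy enrollment". Restrictions fall under "parental report of smoking behavior change (ie, cessation, quit attempts, reduction, and restrictions) served as secondary outcomes".
- Sample Size and Power Considerations sizes the trial on the "difference of SHS home exposure (primary outcome) between the two treatment groups at week 26".
- Primary Analyses again marks home SHS exposure as primary and gives it a t test, with a log transformation or Wilcoxon test if the data are non-normal. Adoption of home restrictions gets a chi-square or Fisher exact test.

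The abstract and the Results section both report that analyses are complete and interpretation is in progress.

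**The concern.** A ban reported by the mother and checked against a dosimeter is a different variable from a change in nicotine concentration. One is binary and partly self-reported; the other is continuous and objective. The article assigns them different tests, and the same construct, home restriction, is primary in one place and secondary in two others.

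The primary outcome fixes which result carries the trial's confirmatory claim. This article is a public record against which the results will be read, and many readers will see only its abstract. With analyses finished, a report that leads with either outcome could cite the article in support, and a critic could cite the same article to say the outcome had been changed. The article gives no means of settling that.

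**Working it through.** **1. Which outcome each section makes primary**

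| Section | Air nicotine (continuous) | Home restriction (binary) |
|---|---|---|
| Abstract, Methods | not listed as an outcome | primary |
| Study Design | primary | secondary |
| Primary and Secondary Outcomes | primary | secondary |
| Sample Size | primary, powered | used only to derive the nicotine means |
| Primary Analyses | primary, t test | chi-square or Fisher |

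The conflict is one abstract sentence against four body sections.

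**2. The plan's own power figure**

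The Sample Size section states: "The power calculation was based on two-sided, two-sample *t* test assuming a type I error of 0.05" and "A total sample size of 180 (90 per treatment group) was determined to achieve 85% power". Its other inputs are means of 1.15 (SD 1.58) and 1.89 (SD 1.68) μg/m³.

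- Difference: 1.89 − 1.15 = 0.74.
- Pooled SD: √((1.58² + 1.68²)/2) = 1.631.
- Standardized difference: 0.74/1.631 = 0.454.
- Normal approximation, 90 per arm: 0.74/(1.631 × √(2/90)) = 3.044; 3.044 − 1.960 = 1.084; power Φ(1.084) = 86.1%.
- Exact noncentral t: 85.7%.
- Needed for 85% power: 88 per arm (normal) or 89 (exact t).

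The stated 85% with 90 per arm reproduces. It belongs to air nicotine.

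**3. Power if the abstract's outcome were primary**

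The article states none. Its only relevant inputs are the assumed ban adoption rates, 55% and 25%, which it does not describe as dosimeter-verified. Taking them as verified rates is an assumption.

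Power = Φ[(|p₁ − p₂| − 1.96 √(2p̄(1 − p̄)/n)) / √((p₁(1 − p₁) + p₂(1 − p₂))/n)]

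With p₁ = 0.55, p₂ = 0.25, p̄ = 0.40 and n = 90:

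- Null standard error: √(0.48/90) = 0.0730.
- Alternative standard error: √(0.435/90) = 0.0695.
- (0.30 − 1.96 × 0.0730)/0.0695 ≈ 2.26, so power is 98.8%.
- Needed for 85% power: 47 per arm, or 53 with continuity correction.

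Verified rates could be lower than reported ones. Holding control at 25% with 90 per arm:

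| Intervention rate | Power |
|---|---|
| 55% | 98.8% |
| 47% | 87.4% |
| 46% | 84.3% |
| 45% | 80.8% |
| 40% | 57.6% |

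Power for the abstract's outcome could therefore lie well above or well below the planned 85%.

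**4. Is the abstract's outcome defined elsewhere?**

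The Outcomes section measures restrictions with one three-level survey question. The only dosimeter threshold in the article is the 0.02 μg/m³ limit of detection, which is used for baseline eligibility. No section says what reading confirms or refutes a reported ban.

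**The case against.** The best defence is that only one sentence is out of line. Four body sections agree on dosimeter-measured nicotine, the sample size is computed for it and reproduces, and nothing calculated in the plan is wrong. That stands. It narrows the point to abstract against body and indicates which reading is probably intended. It does not remove the contradiction, because the abstract is part of the public record and no typographical slip turns a nicotine change into a verified ban.

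It is also fair to say that 98.8% was never a planned power. The 55% and 25% enter only as the source of the assumed nicotine means, so the figure is conditional.

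A reader might infer three further faults that the text does not support:

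- **Different missing-data rules for the two outcomes.** The rule counting dropouts as smokers belongs to the cessation measure. The missing-data section gives a zero change score for absent week-26 data. No separate rule for bans is stated.
- **A familywise error of 5% to 9.75%.** The upper figure is 1 − 0.95², which assumes independent tests. The article derives the nicotine difference from ban adoption, so it treats the two as linked, and independence is not a strict upper bound in any case. More importantly, no section plans to claim success on either outcome.
- **Two different clocks.** The abstract and Study Design count from randomization, the Outcomes section from enrollment. But 195 are described as enrolled and 98 + 97 = 195 as randomized, so the two terms may mean the same event.

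**Conclusion.** The contradiction holds and should be corrected. The article gives the primary label to a binary restriction outcome in the abstract and to continuous air nicotine in the body, with different tests. Only air nicotine has a stated power (85%, reproduced at 85.7%). The abstract's outcome has neither a power statement nor a verification rule. Its power would be 98.8% if 55% and 25% were verified rates, and 81% or 58% if the intervention rate were 45% or 40% with control at 25%.

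The conclusion that the outcomes conflict does not depend on those power figures. The sample size is not in error, and the documents give no ground for alleging that the primary outcome was switched. What they show is that, with analyses complete, the article alone does not settle which result is confirmatory.

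**What to change.** 1. Confirm the prespecified primary outcome from a record that predates the analyses, and cite that record. Rewording the abstract without this step would itself be a choice made after the data were analyzed.
2. State that single outcome in the abstract and every body section. The body and the sample size calculation point to home air nicotine by dosimeter at week 26, tested alone at two-sided 0.05. If the record says otherwise, the body and the power section need correcting instead.
3. If air nicotine is confirmed, label home smoking restriction as secondary. Call it dosimeter-verified only if the prespecified verification rule is given; otherwise describe it as self-reported.
4. Use one time origin in the abstract, Study Design and Outcomes, matching how visits were actually timed.

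The cost is a check of existing records and a text correction. No new data or participants are needed. If air nicotine is confirmed, the authors give up presenting the restriction result as primary.

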**Results:**

Data collection and analyses are complete, and the results are being interpreted.

**Conclusions:**

The study protocol describes the development of a novel community-based controlled trial designed to examine the efficacy of biomarker feedback documenting home and child exposure to SHS on parental smoking behavior change.

**International Registered Report Identifier (IRRID):**

RR1-10.2196/12654

## Introduction

Secondhand smoke (SHS) is a Class A carcinogen with no safe level of exposure. It is estimated that approximately 66% of children aged 3-11 years are exposed to SHS [1]. The human and economic costs of children’s exposure to SHS are staggering and result in 400,000-1 million additional asthma attacks [2], 22,000 asthma-related hospitalizations, 1-3 million outpatient visits due to middle ear disease [2,3], and 100,000-165,000 ear tube operations each year [3,4]. Children exposed to SHS also have higher rates of behavioral and cognitive effects, including attention deficit and hyperactivity disorder [5]. Tobacco use in the home also contributes to 10,000 burn-related outpatient visits and 600 hospitalizations annually [3]. After including increased sudden infant death, exposure to SHS annually contributes to 5000 child deaths and medical costs in excess of US $10 billion [3].

Nearly 19.1 million US children younger than 18 years live in households that have a smoker, making them the most exposed age group [6]. Children are unable to avoid the main source of exposure—often, their close relatives who smoke at home. Furthermore, children have the strongest evidence of harm attributable to SHS [7]. Lower-income children suffer disproportionately from the consequences of SHS exposure, with well-documented higher rates of sudden infant death and asthma [6]. Although the roots of these disparities are complex (eg, poor housing conditions and environmental allergens), exposure to SHS is a prominent and quickly reversible cause of excess morbidity and mortality.

Two reviews detailing the literature on home SHS reduction [8-10] found mixed results. The majority of the studies combined simple self-help materials (ie, instructional pamphlets) with brief intervention (typically one session and as short as 2 minutes) delivered by a nurse or physician. A series of studies of these limited interventions [11-15] reported similar changes in home smoking bans and child’s exposure in intervention as compared to non-intervention control. Compared to the uniform failure of simple self-help or brief SHS reduction interventions, more comprehensive multicomponent interventions have shown more positive effects [16-19]. Results of these trials indicate that multisession, home-based interventions involving motivational counseling might prove more effective. Although the findings for multisession counseling interventions are more promising than self-help or brief interventions, more powerful interventions are clearly needed. Only a few studies have utilized objective laboratory-based assay findings (ie, biomarkers) of children’s exposure to tobacco toxins to reduce home SHS. Initial trials provided this feedback in the form of mailed brochures [20] or brief physicians phone calls to inform parents [21] about the results of biomarker testing on the child and reported null findings. Biomarker feedback seems to be more promising when combined with a more intensive counseling intervention [22,23].

The potential promise of biomarker feedback aimed at reducing home SHS exposure contrasts with a body of literature indicating its limited efficacy on smoking behavior change when used to provide a smoker with objective assay results documenting his/her own exposure to tobacco toxins [24,25]. One possible explanation for the observed discrepancy is that messages that convey risk to a child exposed to parental smoking may be more motivating than messages that convey direct risk to the individual smoker. In their reviews, McClure and Bize [24-26] speculate the other reasons why biomarker feedback to the smoker has not demonstrated a significant impact on behavior change. The first possibility is that the biomarker feedback may not have been sufficiently motivating. This could occur if the risk is perceived to be immutable (ie, a genetic risk factor) or the individual did not understand the meaning of the biomarker on which the feedback was based (ie, meaning of cotinine). Another possibility is that the individual may discount the message because he/she does not trust the source delivering the feedback. A classic line of research demonstrates that attitude change is greater when the communicator is viewed as credible, trustworthy, similar to the recipient, and not trying to change the recipients’ beliefs [27,28]. Finally, elevating the perceived risk of future health consequences (the target of biomarker feedback) alone may be insufficient to bring about behavior change.

Hecht and colleagues [29] documented high levels of one of the most potent tobacco-specific carcinogens—NNAL (4-[methylnitrosamino]-1-[3-pyridyl]-1-butanol—in the urine of children exposed to SHS. This discovery raised substantial concerns within both the scientific and the public health communities, but this information has yet to be utilized to educate parents or caregivers about children’s exposure to cigarette smoke in their homes.

We attended to each of these potential limitations in the design of project STARS (Start Taking Action to Restrict Smoking). STARS is a community-based, randomized trial designed to assess the efficacy of providing culturally sensitive biomarker feedback and objective data about the level of SHS in the home environment to a mother or female caregiver in order to motivate the implementation of home smoking restrictions. Feedback on their child’s exposure to known carcinogens (“cancer causing chemicals”) in tobacco may be more intrinsically motivating than information on other markers of SHS exposure (ie, cotinine). This information was presented by a trusted source (ie, community health workers and a counselor from the participants’ local community) as part of a comprehensive intervention informed by Motivation and Problem Solving (MAPS) [30] counseling designed to empower participants to make positive changes in their own behavior and home environment. In addition, although not included in feedback to parents, we collected and analyzed dust from participants’ homes to examine whether “thirdhand tobacco smoke” (THS) or the residue remaining on surfaces after a cigarette is extinguished could be detected in measurable quantities. The objective of this paper is to detail our approach to building and executing this complex, community-based intervention designed to speed the translation of science from the “bench” to the “community” in order to reduce tobacco toxin exposure among children.

## Methods

### Study Design

Figure 1 presents an overview of the study. The primary aim of this two-group, community-based randomized trial (ClinicalTrials.gov NCT01574560) was to assess the efficacy of providing mothers with biomarker feedback documenting their child’s tobacco toxin exposure on reduction of home exposure to tobacco toxins. Once eligibility was determined, participants were randomized to either the intervention arm (biomarker feedback) or the control arm (health education). At baseline, participants in both groups received a series of health education brochures designed to provide information on the dangers of SHS and THS, strategies for managing parenting stress, and tips to assist in a quit attempt. Participants randomized to the active condition were given the results of their child’s urine analyses of nicotine, cotinine, and NNAL as well as the results of the home nicotine dosimeter. They also received five motivational interviewing counseling sessions, approximately 30 minutes in length, spread over 12 weeks. At each counseling session, participants were offered nicotine replacement therapy in the form of gum or lozenge (4 mg). The primary outcome was reduction in home ambient nicotine levels, objectively measured by the passive nicotine dosimeter [31] at 6 months after randomization. Secondary outcomes included child exposure to tobacco toxins measured by urinary levels cotinine, nicotine, and NNAL (a metabolite of NNK, which is a tobacco-specific carcinogen known as 4-[methylnitro-samino]-1-[3-pyridyl]-1-butanone) and a parental report of cigarettes smoked in the home and home smoking policies. Additional aims included identifying potential mediating and moderating effects of demographic variables and psychosocial and tobacco use characteristics.

**Figure 1 figure1:**
[figure not shown]
Overview of the study procedures. MAPS: Motivation and Problem Solving.

### Study Setting

The work in this trial was guided by the principles of community-based participatory research (CBPR). CBPR is an approach to research and community engagement that recognizes that the knowledge, expertise, and resources of communities often determine the success of research projects. Thus, we fully engaged our community partner in the research process [32]. Fundamental characteristics of CBPR include collaboration, empowerment, colearning, and community capacity building. An overarching key to the success of CBPR partnerships is the development of authentic partnerships. In project STARS, we partnered with a community health center serving a predominantly lower-income, African American community.

Our selected community health workers were community members chosen by our community partner agency and hired to engage the community in efforts to decrease children’s exposure to tobacco toxins. As liaisons between community members and the research team, they provided cultural mediation and peer social support, advanced culturally appropriate and accessible health education and information, and increased participant access to health services when indicated [33-36]. The approach of using community health workers who are ethnically, socioeconomically, and experientially indigenous to the community has been used in prior cessation trials with success [29,37,38]. Further, evidence of the effectiveness of using community health workers in interventions targeting child health is strong. According to a 2005 Cochrane Review [39-41], community health workers are well positioned to reinforce messages and aid in the protection of children from SHS exposure.

Our community partner provided two full-time community health workers employed by the organization. The community health workers were certified health educators trained to work with individuals who may have difficulty understanding medical providers due to cultural or language barriers. Their role was to recruit, enroll, and conduct all assessment visits. The community health workers were female and indigenous to the target community, adding a source of relatedness and trust for participants. Our community health workers were also trained to interact with participants to enhance autonomy, competence, and relatedness in order to empower self-determined decision making in response to child biomarker feedback. Community health workers are thought to increase the relatedness of the intervention and positively influence message salience and comprehension, clarifying the perceived benefits of adopting home smoking bans.

The research team was located in offices in close proximity to the participant target area. In addition to the two CHWs, the research team was composed of a project coordinator, one full-time counselor from the community, one full-time research assistant, and multiple student workers, many of whom were also from the target community.

